**1 INTRODUCTION AND BACKGROUND**

The first pancreas transplantation (PTx) was performed in Minnesota in 1966 by Kelly

and colleagues (1). In recent years the number of procedures has grown considerably worldwide, and is now a well-established treatment option for patients with diabetes mellitus with and without concomitant diabetic End-Stage Renal Disease (ESRD) (2-4). The indication for PTx is advanced and/or badly controlleddiabetes mellitus (”brittle” diabetes, severe hypoglycemic episodes,”unawareness”, etc). Solitary pancreas transplantation (SPT; without concomitant kidney transplantation) is usually classified as PTx alone (PTA), PTx after kidney transplantation (PAK) or PTx after islet transplantation (PAI). Kidney transplantation of the diabetic uremic population increases survival compared to long-term dialysis (5, 6). Transplant options for patients with diabetic end-stage nephropathy include simultaneous pancreas-kidney (SPK), live donor kidney (LDK) and deceased donor kidney (DDK) transplantation. SPK transplantation relieves not only the patient’s uremia, but also alleviates the hyperglycemic state of diabetes. Large international patient registries show that patient survival rates after SPK have reached more than 95% at 1 year and 87% at 5 years post-transplant, respectively (2). Nevertheless, PTx as treatment for type 1 diabetes has not gained the same popularity as transplantation of other organs, partly because PTx have been associated with a high rate of surgical complications; particularly bleeding, thrombosis and exocrine leakage. Furthermore, there has been a lack of reliable, non-invasive rejection monitoring instruments, and the invasive, percutaneous pancreas biopsies have traditionally been associated with a high rate of complications (exocrine leakage, bleeding).

The difficulties encountered with PTx have to some extent been compensated by a very selective attitude towards the donors, but thereby making pancreas grafts a scarce resource. In contrast to other abdominal transplantations such as liver transplantation (LTx) and kidney transplantation (KTx), where repeated biopsies have been used for immunosurveillance, percutaneous biopsies of the pancreas-graft have traditionally been avoided due to a high rate of biopsy-related complications (exocrine leaks/fistulas and bleeding episodes). Thus, fear of acute rejections and lack of adequate rejection markers, have led to a rather intensive immunosuppressive load in PTx recipients.

Solitary pancreas transplantation (SPT) has traditionally been subjected to even higher complication and rejection rates, with inferior graft and patient survival - thus favoring the combined SPK procedure. This has been attributed to an even worse rejection monitoring capability, without a”reporter”/sentinel allograft kidney. No biochemical markers have proven to be effective in rejection surveillance.

Pancreas graft thrombosis is a feared complication in the postoperative course, partly due to the oversized vessels used (coeliac trunk/superior mesenteric artery/portal vein) in conjunction with the low blood flow through an isolated pancreas graft. In the native setting, these vessels also serve the intestines and spleen. Therefore, PTx poses a delicate balance between thrombosis and bleeding complications.

*End stage type 1 diabetes is a devastating chronic disease. PTx offer long term insulin-independency. Efforts should be made to define robust patient selection criteria and offer eligible patients insulin-independency before severe diabetic complications appear.*

**1.1 The Norwegian experience**

PTx is performed at one single national center in Oslo, and from 1983 to date 300 procedures have been performed (7-11). In recent years, the activity has increased; 22 were performed in 2011 and 28 in 2012. Approximately 9 out 10 PTx’s have been SPK’s, hence only about 10% have been SPTs. In the first period from 1983 through 1987, a duct-occluded segmental pancreas was used for transplantation. From 1988, the whole pancreas graft was used, and the exocrine secretion was drained by anastomosing the duodenal segment to the urinary bladder. This technical solution was chosen partly because it offered some sort of rejection monitoring, by urine amylase counts and cystoscopic pancreas biopsies. However, many patients suffered from chemical cystitis and metabolic acidosis, due to loss of bicarbonate. In 1998 the urinary bladder anastomosis was abandoned, in favor of the more physiological enteric anastomosis, the duodenal segment being connected to the proximal jejunum. However, this solution offered even less options to monitor upcoming rejections, as percutaneous biopsies was mostly avoided due to the previously mentioned hazards.

We have recently examined (12) all PTx’s performed at our hospital during 2006-2010 (n=61; 59 SPK, 2 PTA). Our overall surgical complication rate has decreased from earlier years, but we still suffer a substantial rate of reoperations (about 30% of patients), mainly caused by exocrine leakage, bleeding and vein thrombosis. When comparing the populations with or without reoperation, higher donor age had a significant negative impact. No significant effect of donor age on graft survival was observed. There was a tendency towards better results in female recipients, both regarding surgical complications and graft survival. The rejection rate (altogether about 30%) was significantly higher in the graft loss group, and reoperations were insignificantly associated with graft loss.

From late 2011 and up to date, several measures have been implemented to improve outcome and reduce the rate of surgical complications. In line with most Tx centers in Scandinavia, we have switched the prophylactic anticoagulation treatment from our traditional Macrodex® regime to a Fragmin® regime. Several surgical/technical changes have also been implemented during recent years; tentatively more atraumatic graft procurement, preserving the entire coeliac arterial axis including the gastroduodenal artery, obtaining a long portal vein to reduce the need for elongation, as well as extended in situ dissection by means of LigasureTM. Due to the conventional lack of rejection monitoring parameters, we launched an investigatory surveillance program, with protocol biopsies of the duodenal segment via double balloon enteroscopy (13). The impact and value of this program has yet to be investigated. Previous reports have described separate rejection of the pancreas or kidney in the SPK setting, and the gold standard for proving rejection of the pancreas is undoubtedly a biopsy of the pancreas itself. This encouraged us to further develop techniques for better surveillance, such as endoscopic transduodenal ultrasound-guided biopsies of pancreas (EUSBP). Inferior outcome of PTA and lack of valid tools for immunosurveillance in the absence of a simultaneous kidney graft, have led some centers to evolve the duodeno-duodenostomy (DD) for drainage of the exocrine pancreas, making the EUSBP possible. There are many theoretical advantages with the DD, especially regarding rejection surveillance, and we have recently adopted this technique. The endoscopic access afforded by the DD also makes it possible to stent the pancreatic duct in case of exocrine leakage.

Though, in recent years we have experienced a very low incidence of complications with the conventional percutaneous ultrasound-guided pancreas biopsy. In our latest, retrospective study (Horneland et al., Am J Transpl; in press), focusing on the duodenoduodenostomy, there were no complications among 18 percutaneous pancreas biopsies performed.

**1.2 Immunosuppressive therapy**

Over time, the induction therapy and maintenance immunosuppressive protocols have changed. From 1983 to 2000, all recipients received triple immunosuppressive regimens with cyclosporine, azathioprine and prednisolone (CS). During the last part of the 1990’s azathioprine was substituted by Mycophenolate mofetil (MMF), and cyclosporine was substituted by tacrolimus. After 2000, the immunosuppression has been intensified by induction therapy both for PTx (Antithymocyte globulin (ATG)) and for kidney transplants alone (basiliximab). Thus in recent years, PTx recipients have received a quadruple immunnosuppressive regimen, that includes tacrolimus, MMF, CS and ATG. The dosage of ATG has been directed by T-cell counts.

**1.3 Rejections/Donor-specific antibodies (DSA)**

During recent years, with the quadruple immunnosuppressive regimen, our biopsy-verified rejection rate has been about 30% (12).

In this study we will follow the routine protocol for treatment of rejections; primarily more CS (5-8 doses of SoluMedrol), secondarily more ATG (2-5 doses; T-cell directed)

A recent study (14) assessed the role of post-Tx HLA antibody monitoring in the surveillance of PTx recipients, and the impact of DSA. Four hundred thirty-three PTx’s were performed at the Oxford Transplant Centre (317 SPK/116 Sol-PTx). It was demonstrated that 39.8% of patients developed de novo HLA antibodies, of which 36.9% were de novo *DSA*. The development of antibodies to donor HLA, but not to nondonor HLA, was significantly associated with poorer graft outcomes, with 1- and 3-year graft survival inferior in SPK recipients, and interestingly even more so in Sol-PTx recipients. In a multivariate analysis, development of de novo DSA emerged as a strong independent predictor of pancreas graft failure.

These findings have urged us to investigate de novo DSA development in the present study.

**1.4 Graft monitoring with microdialysis catheters**

As stated in the previous paragraphs the complication rates following pancreas transplantation are high. Except maybe for severe hemorrhage, all complications have in common that they are difficult to detect. Accordingly, there is an emerging need for better monitoring of pancreas transplants. We consider that further improvement of surgical techniques and immunosuppressive protocols rely upon better monitoring tools.

Microdialysis is a technique, which enables close to ‘real time’ monitoring of tissues and organs of interest. Depending on the membrane’s pore size, metabolic substances (lactate, pyruvate, glucose and glycerol) and/or mediators of inflammation (cytokines, chemokines and complement factors) are sampled in a feasible way (15). So far, the method’s ability to detect brain ischemia is the best validated (16). In the United States clinical application is so far restricted to neurointensive care units, as only the brain catheter (CMA 70, CMA Microdialysis AB, Stockholm, Sweden) is approved by the Food and Drug Administration for clinical use. However, there are more than 2000 clinical reports on microdialysis catheters, and in Europe the catheters are Conformité Européenne marked for a wider range of indications.

We have done extensive clinical observation trials using microdialysis catheters in liver transplanted patients and we have inserted more than 200 catheters in hepatic tissue without experiencing any major complications (17-21).Graft thrombosis has been detected almost in ‘real time’ as elevated intrahepatic lactate and lactate to pyruvate ratio. Rejection has been detected several days before the rise in conventional blood markers (bilirubin and transaminases) by elevated lactate and with unchanged lactate to pyruvate ratio. Acute cellular rejections were detected with more than 80 % sensitivity and specificity. Ischemic complications like hepatic artery thromboses have been detected with 100 % sensitivity and specificity. We also revealed potentially specific biomarkers for ischemia (complement factor 5a) and rejection (CXCL-10) (19) . We have now implemented microdialysis as routine standard of care in *pediatric* liver transplants.

We are also investigating the potential role of microdialysis in monitoring patients who have undergone Whipple’s operation for pancreatic or duodenal cancer. Preliminary results show that leakages in the pancreaticojejunostomy can be detected at a very early time point, by increased concentrations of glycerol in samples collected from catheters positioned close to the enteroanastomosis.

**2 OBJECTIVES OF THE STUDY**

Several studies have shown acceptable results after PTx by substituting ATG with basiliximab (22-26), which is considered to convey a considerably lower number of adverse events. However, our experiences with ATG in PTx (introduced in 2004) are good, and our presumably gentle way of administrating the drug – directed by T-cell counts - is in fact unique (12). The potential advantages of reducing the overall corticosteroid (CS) load is obvious, as CS is a well-known pro-diabetic agent and causes severe long term adverse effects (22).

On this background, we have very recently reduced our CS dosing (in the routine protocol) to a level corresponding to our Kidney Tx protocol (valid since 2009). Thus*, we intend to prospectively investigate and compare a single cohort of our present PTx immunosuppressive protocol with previous (historical) cohorts.*

The rationale for the study is that; *i*) a high immunosuppressive load, and in particular CS, may be partly responsible for the high rate of PTx associated complications/reoperations; *ii*) a high immunosuppressive load is related to infectious complications; *iii*) improved PTx rejection surveillance by DD and EUSBP allows a lower-graded immunosuppressive protocol; iv) evaluating the surgical and medical measures made to our PTx program during the past two years

**2.1** **Primary objectives**

- Compare the incidence of *acute rejection episodes* at 6, 12, 36 and 60 months after pancreas transplantation, between our single prospective cohort with lower CS vs a historic, retrospective control group (PTx performed during 2011-2013). The incidence of rejection is defined as the fraction of patients in which rejections episodes (one or more) have been proven by biopsies. For SPK rejection in eitherorgan, pancreas or kidney, counts.
- Compare the incidence of *surgical complications*, involving reoperations and reinterventions, between the prospective study group and retrospective control group.

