**2.7 Pancreas transplant monitoring with microdialysis catheters**

- At end of surgery totally three microdialysis catheters will be inserted. The catheters membranes have a 100 kDa pore size, an outer diameter of 0.6 mm and a length of 30 mm. A secure thread is positioned 60 mm from the tip (CMA 65, CMA Microdialysis AB, Stockholm, Sweden).The left abdominal wall will be punctured at three different locations close to each other by a hypodermic needle (Sterican® 14G X 3 1/8 “, B. Braun AG, Melsungen, Germany) through which the microdialysis catheter will be led. After removing the hypodermic needle one microdialysis catheter will be sutured to superfluous connective tissue on the pancreas graft, one will be sutured to the fascia of the right psoas muscle implying that the pancreas graft will be in direct contact with the catheter, and one catheter will be secured close to the duodenoduodenostomy. The catheters will be secured to the skin using a 4.0 thread. Each catheter will be perfused with 6 % hydroxyethyl starch at a rate of 1 µL/minute by microinjection pumps (CMA 107, CMA Microdialysis AB, Stockholm, Sweden), and the samples will be collected in microvials (CMA Microdialysis AB, Stockholm, Sweden)
- Postoperatively the microdialysis samples will be analyzed every second hour at the bedside for glycerol, glucose, lactate, and pyruvate using a microdialysis analyzer (Iscus Flex, CMA Microdialysis AB, Stockholm, Sweden).The lactate to pyruvate ratio will be calculated. Thereafter the samples will be frozen to -20°C and later to -80°C.
- Since this study is the first of its kind and threshold values for detecting e.g. pancreatic graft ischemia, leakages, and rejections have not been established we will not implement e.g. a decision tree in the protocol. However, since not only the physicians responsible for the studies, but also the nurses at ward have substantial experience with the microdialysis method, we expect that deviations from the normal course may lead to prescription of e.g. ultrasound Doppler examinations, and that graft complications thereby may be detected earlier. From a purely scientific point of view one could argue that blinding nurses and physicians for the results would be appropriate. However, we consider this not feasible since the researchers also are responsible for treating the patients and it is important that they have immediate access to the data to reveal e.g. inappropriate sampling.

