**10.3 Statistical methods in data analysis**

- The primary evaluation criteria ‘Incidence of rejection’ and ‘Rate of surgical complications’ will be evaluated for several populations:

- All patients who receive at least one dose of study medication, defined as the ‘Intention-to-Treat’ population.

- All patients who complete 12 months of intended study medication, defined as the ‘Intention completed’ population.

The analysis of these categorical parameters will consist of:

1. Comparisons of groups using the Fisher exact test.

2. Confidence intervals of 95% of the percentage of incidence of these

events.

- The loss of grafts and deaths will be analysed by the Kaplan-Meier method for estimating the time to events.
- Continuous (non-categorical) variables will be analyzed by student t-tests and chi-square tests.
- Microdialysis data are typically non-normally distributed. We will therefore use the Wilcoxon Signed rank test for repeated measurements and the Mann-Whitney U test for comparison of groups. We will also use linear mixed model analyses on log10 transformed data for repeated measurements. Receiver operating curves and contingency tables will be used to explore sensitivity and specificity.
- Any other methods that are not planned can be considered as alternative methods.

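### The 2011-2013 control group spans programme changes begun in late 2011, so the comparison framed as a steroid-dose effect also carries those changes, and it dilutes the evaluation of the changes themselves

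*Protocol*

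**What the plan says.** Section 2.1 defines the control group by calendar year. Rejection is to be compared "between our single prospective cohort with lower CS vs a historic, retrospective control group (PTx performed during 2011-2013"). Surgical complications, the other primary endpoint, are compared between the same two groups.

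Section 1.1 describes a programme in change over those years: "From late 2011 and up to date, several measures have been implemented to improve outcome and reduce the rate of surgical complications". It names the anticoagulant: "we have switched the prophylactic anticoagulation treatment from our traditional Macrodex® regime to a Fragmin® regime". It adds that "Several surgical/technical changes have also been implemented during recent years; tentatively more atraumatic graft procurement", followed by further changes in dissection and vessel handling. On duodeno-duodenostomy (DD) it says: "There are many theoretical advantages with the DD, especially regarding rejection surveillance, and we have recently adopted this technique". For the study cohort, section 2.7 takes DD as given, since "one catheter will be secured close to the duodenoduodenostomy".

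Section 2 gives two aims that bear on this point. Rationale (i) is that the immunosuppressive load, steroids in particular, may contribute to complications and reoperations. The other is "iv) evaluating the surgical and medical measures made to our PTx program during the past two years".

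Section 10.3 analyses both primary endpoints by "Comparisons of groups using the Fisher exact test". Section 2.5 lists the characteristics to be related to outcome. All are donor or recipient traits; anticoagulant, drainage type, procurement era and steroid schedule are not among them.

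**The concern.** A historical comparison can be read as the effect of one change only if the other parts of care were the same in both periods. Here several were not. At least some of the other changes were made in order to lower the surgical complication rate, which is itself a primary endpoint.

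The protocol does lean on a steroid reading. Section 2.1 labels the study cohort by its lower steroid dose. Section 10.1 describes the controls by their high dosing and argues the expected direction of the complication rate from the lighter regimen. Section 10.4 makes a doubling of either rate relative to the controls a reason to consider discontinuing the study and the routine steroid dosing. A difference due to anticoagulation or surgical technique could therefore be taken as evidence about steroids, or could mask such evidence.

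The opposite problem affects rationale (iv). Evaluating the measures requires controls without them, and part of this control group already had them.

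**Working it through.** **1. The plan's own figures.** Section 10.2 uses N = [Pn(1 - Pn) + Ps(1 - Ps)] x c / (Pn - Ps)^2 per arm.

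| Endpoint | Pn | Ps | c | Calculation | Result | Plan |
|---|---|---|---|---|---|---|
| Rejection | 0.30 | 0.40 | 7.9 | (0.21 + 0.24) x 7.9 / 0.01 | 355.5 | 355 |
| Complications | 0.30 | 0.20 | 7.9 | (0.21 + 0.16) x 7.9 / 0.01 | 292.3 | 292 |
| Rejection | 0.30 | 0.60 | 5.3 | (0.21 + 0.24) x 5.3 / 0.09 | 26.5 | 27 |
| Complications | 0.30 | 0.15 | 5.3 | (0.21 + 0.1275) x 5.3 / 0.0225 | 79.5 | 80 |

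The figures reproduce. For complications they give a yardstick: differences of 10 and 15 points are what the plan considers. The 0.30 comes from the centre's 2006-2010 series (61 transplants, section 1.1), which ends before the control window opens.

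**2. What is dated and what is not.**

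| Item | Date in the protocol | Study cohort |
|---|---|---|
| Control window | 2011-2013 | not applicable |
| Macrodex to Fragmin | among the measures from late 2011 onward | changed regimen, by inference |
| Procurement and dissection | recent years only | changed practice, by inference |
| DD drainage | recently, no date | presupposed by section 2.7 |
| Steroid reduction | very recently, no date | yes |

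The window opens before late 2011 and continues after it. For anticoagulation the overlap follows from the text. For drainage it is a strong inference, and for procurement the text leaves it open.

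**3. What the pooled difference estimates.** Let m be the drop in complication rate due to a measure, s the drop due to the steroid reduction, and g the share of controls who already had the measure. Assume additive effects and that every study patient had the measure. Then

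control rate - study rate = (1 - g) x m + s.

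Read as a steroid effect, the difference is off by (1 - g) x m. Read as an evaluation of the measure, it shows only the fraction (1 - g) of m, with s added. The protocol does not give g, so one observed difference cannot separate the two terms.

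**4. An illustration of size.** Section 1.1 gives 22 transplants in 2011 and 28 in 2012. The 2013 count is not given; assume 20 to 30. The control group is then 22 + 28 + 20 = 70 to 22 + 28 + 30 = 80, and the 2011 share is 22/70 = 31% to 22/80 = 28%. Treat all 2011 patients, and no later ones, as lacking the measure. If it was in place by late 2011, this is an upper limit on the share; if it came later, the share is larger. With an assumed m of 10 points and s = 0:

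- 0.31 x 10 = 3.1 points
- 0.28 x 10 = 2.8 points

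The spurious difference is about 3 points. For other values of g, with the measure taking the rate from 0.30 to 0.20 and no steroid effect:

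| g | Control rate | Apparent difference |
|---|---|---|
| 0 | 0.30 | 10 points |
| 0.25 | 0.275 | 7.5 points |
| 0.50 | 0.25 | 5 points |
| 0.75 | 0.225 | 2.5 points |
| 1 | 0.20 | 0 points |

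**5. Effect on the test.** With 70 per group (assumed), summing the exact probabilities of all pairs of binomial counts with Fisher p < 0.05 gives 4.7% for true rates of 0.23 and 0.20, against 3.1% when both are 0.20. A 3-point bias would seldom produce a significant result by itself. The harm lies in what the estimate is taken to mean.

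**The case against.** The protocol calls itself a single-cohort observational study with a historical control (sections 3 and 10), and rationale (iv) openly includes the other measures. The complications objective in section 2.1 does not carry the lower-steroid label. The statistical analysis plan is not at hand and may contain a stratified or adjusted analysis, so the absence of one from the protocol is no fault. The only part that can be sized from the text is small, and it rests on an assumed effect.

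Most of this stands as a limit on the point, but it does not remove it. Admitting that a study is observational concedes non-randomisation; it does not say what the difference estimates, while sections 10.1 and 10.4 read it through steroid dosing. The control definition and that framing are fixed in the protocol, and a stratified analysis is possible only if the exposures are recorded for each patient.

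Four stronger readings are tempting, and the document supports none of them:

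- **A large bias through DD, approaching the plan's 10-point target.** The date of DD adoption is not given, so any non-DD share of the controls is a guess. Section 1.1 credits DD mainly with better rejection surveillance. It also opens a route for endoscopic stenting, which could add reinterventions. Even the direction is unclear.
- **Rationale (iv) cannot be answered because most controls had the measures.** Partial exposure dilutes the comparison but does not void it, and the exposed share is unknown for procurement and DD.
- **Some controls may have had the lower steroid dose.** Section 2 says the reduction was very recent and section 10.1 describes the controls as high-dose. This deserves confirmation, but it is not a demonstrated fault.
- **A lower complication rate will be credited to steroids.** No sentence in the protocol commits to that; the framing only invites it.

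**Conclusion.** The point holds in limited form. The control window opens before and runs through changes begun in late 2011, so the pooled comparison combines the steroid reduction with at least the anticoagulant switch, and probably with drainage and procurement changes. The same overlap weakens the evaluation of those measures.

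Neither the size nor the direction of the bias can be fixed from the document. The figure of about 3 points rests on four assumptions: 20 to 30 transplants in 2013, a measure absent in 2011 and present afterwards, a 10-point effect of that measure, and no steroid effect. It should not be quoted as an estimate.

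The point should be fixed, as a cheap improvement. It is not a reason to hold the study.

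**What to change.** 1. State the date of each change: anticoagulant, procurement and dissection, drainage, and steroid schedule.
2. Record steroid schedule, anticoagulant, drainage type and procurement era for every study and control patient, and tabulate them by group.
3. Confirm that the control patients received the previous steroid schedule.
4. Beside the pooled comparison, prespecify a steroid comparison restricted to, or stratified by (for example Mantel-Haenszel), controls with the same anticoagulant as the study cohort and, where overlap exists, the same drainage.
5. For rationale (iv), compare patients treated before the measures with those treated after them, descriptively. The 2006-2010 series and early 2011 could supply the former group, at the price of more calendar drift.
6. State that the pooled result against 2011-2013 compares whole programmes and is not an effect of steroid dose. Make the same qualification where section 10.4 uses the comparison.

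The cost is protocol wording and a few variables that should be obtainable from the single centre's own surgical and hospital records. The downside is a smaller matched control set and wider intervals, in a study that already accepts 60% power. If DD and the steroid reduction arrived together, there may be no overlap on drainage. That part of the confounding should then be stated as unresolvable.
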